**Study Day 1 (Mali only)**

1. Perform basic history and focused physical examination (including injection site), emphasizing examination of any acute complaints.
2. Record vital signs.

**Study Day 2 (Mali only)**

1. Perform basic history and focused physical examination (including injection site), emphasizing examination of any acute complaints.
2. Record vital signs.

**Study Day 3  $\pm$ 1 Day**

1. Perform basic history and focused physical examination (including injection site), emphasizing examination of any acute complaints.
2. Review memory enhancement card.(US only)
3. Record vital signs.
4. Obtain approximately 10 mL of blood for CBC with differential and platelet count, ALT, and creatinine.
5. Obtain urine for dipstick test (Mali only)

**Study Day 7  $\pm$ 1 Day**

1. Perform basic history and focused physical examination (including injection site), emphasizing examination of any acute complaints.
2. Record vital signs.
3. Obtain approximately 10 mL of blood for CBC with differential and platelet count and serum creatinine (Mali only).
4. Obtain urine for dipstick test.
5. US only: Review Days 0-6 memory enhancement tool.

**Study Day 14  $\pm$ 2 Days**

1. Perform basic history and focused physical examination (including injection site), emphasizing examination of any acute complaints.
2. Record vital signs.
3. Obtain urine for dipstick testing. Obtain urine or serum for  $\beta$ -hCG testing.
4. Obtain approximately 15 mL of blood for CBC with differential and platelet count, ALT, creatinine, anti-AMA1 and anti-MSP142 ELISA.

**Study Day 28  $\pm$ 3 Days**

1. Perform directed history and assessment of any physical complaint.
2. Record vital signs.
3. Obtain urine for dipstick test.

**Study Day 56  $\pm$ 7 (Day of Second Vaccination)**

1. Perform basic history and focused physical examination, emphasizing examination of any acute complaints.
2. Mali only: during the physical examination, study staff will educate the subject regarding signs and symptoms of potential AEs, and indications for use of antipyretics

- (acetaminophen/paracetamol, or ibuprofen) if fever, headache, or malaise occurs.
3. Obtain approximately 40 (35 in Mali)mL of blood for CBC with differential and platelet count, ALT, creatinine, anti-AMA1 and anti-MSP142 antibody ELISA, and B cell studies.
  4. Obtain blood for malaria smear and filter paper collection (Mali only).
  5. For females, obtain a urine or serum sample for  $\beta$ -hCG testing. Ensure that the test is negative before vaccinating; a positive test will exclude the subject from the trial.
  6. Obtain a urine sample for dipstick testing and ensure that protein and blood are no more than trace positive before vaccinating. Should a female subject be menstruating on Day 56, she will not be excluded from vaccination if she has more than trace blood in her urine.
  7. Obtain urine for chloroquine testing (Mali only).
  8. Record vital signs (blood pressure, temperature, heart rate, and respiratory rate).
  9. Administer the vaccine.
  10. Observe for at least 30 minutes after vaccination to evaluate for immediate adverse reactions.
  11. US only: Review of proper use of digital thermometer, injection-site reaction measurement tool, and memory enhancement tool (diary) by study staff during 30-minute post-immunization wait period. Study staff will also discuss signs and symptoms of potential AEs, and indications for use of antipyretics (acetaminophen/paracetamol, or ibuprofen) if fever, headache, or malaise occurs.

#### **Study Day 57 (Mali only) (1 Day after Second Vaccination)**

1. Perform basic history and focused physical examination (including injection site), emphasizing examination of any acute complaints.
2. Record vital signs.

#### **Study Day 58 (Mali only) (2 Days after Second Vaccination)**

1. Perform basic history and focused physical examination (including injection site), emphasizing examination of any acute complaints.
2. Record vital signs.

#### **Study Day 59 $\pm$ 1 Day (3 Days after Second Vaccination)**

1. Perform basic history and focused physical examination (including injection site), emphasizing examination of any acute complaints.
2. Review memory enhancement tool. (US only)
3. Record vital signs.
4. Obtain approximately 10 mL of blood for CBC with differential and platelet count, ALT, and creatinine.
5. Obtain urine for dipstick test (Mali only)

#### **Study Day 63 $\pm$ 1 Day (7 Days after Second Vaccination)**

1. Perform basic history and focused physical examination (including injection site), emphasizing examination of any acute complaints.
2. Record vital signs.
3. Review Days 28-34 memory enhancement tool.
4. Obtain urine for dipstick tests.
5. Obtain approximately 50 mL of blood for CBC with differential and platelet count, serum creatinine (Mali only), and B and T cell studies.

**Study Day 70 $\pm$ 2 Days (14 Days after Second Vaccination)**

1. Perform basic history and focused physical examination (including injection site), emphasizing examination of any acute complaints.
2. Record vital signs.
3. Obtain urine for dipstick testing. Obtain urine or serum for  $\beta$ -hCG testing.
4. Obtain approximately 40 mL of blood for CBC with differential and platelet count, ALT, creatinine, anti-dsDNA, anti-AMA1 and anti-MSP142 antibody ELISA, T cell studies, and GIA.
5. Obtain blood for malaria smear and filter paper collection (Mali only).

**Study Day 84  $\pm$ 3 Days (28 Days after Second Vaccination)**

1. Perform basic history and assessment of any physical complaint.
2. Record vital signs.
3. Obtain urine for dipstick tests.

**Study Day 180  $\pm$ 14 Days (Day of Third Vaccination) (US)**

1. Perform basic history and focused physical examination, emphasizing examination of any acute complaints.
2. Obtain approximately 40 mL of blood for CBC with differential and platelet count, ALT, creatinine, anti-AMA1 and anti-MSP142 antibody ELISA, and B cell studies.
3. For females, obtain a urine or serum sample for  $\beta$ -hCG testing. Ensure that the test is negative before vaccinating; a positive test will exclude the subject from the trial.
4. Obtain a urine sample for dipstick testing and ensure that protein and blood are no more than trace positive before vaccinating. Should a female subject be menstruating on the day of vaccination, she will not be excluded from vaccination if she has more than trace blood in her urine.
5. Record vital signs (blood pressure, temperature, heart rate, and respiratory rate).
6. Administer the vaccine.
7. Observe for at least 30 minutes after vaccination to evaluate for immediate adverse reactions. Review of proper use of digital thermometer, injection-site reaction measurement tool, and memory enhancement tool (diary) by study staff during 30-minute post-immunization wait period. Study staff will also discuss signs and symptoms of potential AEs, and indications for use of antipyretics (acetaminophen/paracetamol, or ibuprofen) if fever, headache, or malaise occurs.

**Study Day 183  $\pm$ 1 Day (3 Days after Third Vaccination) (US)**

1. Perform basic history and focused physical examination (including injection site), emphasizing examination of any acute complaints.
2. Review memory enhancement tool.
3. Record vital signs.
4. Obtain approximately 10 mL of blood for CBC with differential and platelet count, ALT, and creatinine.

**Study Day 187  $\pm$ 1 Day (7 Days after Third Vaccination) (US)**

1. Perform basic history and focused physical examination (including injection site), emphasizing examination of any acute complaints.
2. Record vital signs.
3. Review Days 180-187 memory enhancement tool.
4. Obtain urine for dipstick tests.
5. Obtain approximately 40 mL of blood for CBC with differential and platelet count, and B and T cell studies.

**Study Day 194  $\pm$ 2 Days (14 Days after Third Vaccination) (US)**

1. Perform basic history and focused physical examination (including injection site), emphasizing examination of any acute complaints.
2. Record vital signs.
3. Obtain urine for dipstick testing. Obtain urine or serum for  $\beta$ -hCG testing.
4. Obtain approximately 40 mL of blood for CBC with differential and platelet count, ALT, creatinine, anti-dsDNA, anti-AMA1 and anti-MSP142 antibody ELISA, B and T cells, and GIA.

**Study Day 210  $\pm$ 3 Days (US)**

1. Perform directed history and assessment of any physical complaint.
2. Record vital signs.
3. Obtain urine for dipstick testing.

**Study Day 270  $\pm$ 14 Days (US)**

1. Perform directed history and assessment of any physical complaint.
2. Record vital signs.
3. Obtain urine for dipstick testing.
4. Obtain approximately 5 mL of blood for anti-AMA1 and anti-MSP142 antibody ELISA.

**Study Day 360  $\pm$ 14 Days (US)**

1. Perform directed history and assessment of any physical complaint.
2. Record vital signs.
3. Obtain urine for dipstick tests.
4. Obtain approximately 50 mL of blood for anti-dsDNA, anti-AMA1 and anti-MSP142 ELISA, GIA, and T and B cell studies.

**Study Day 720  $\pm$  14 Days (US)**

For US volunteers, if the volunteer consents, a phone call will be made to ask whether the volunteer has developed any autoimmune disease since his or her participation in the study. The volunteer will also be asked if he or she has been hospitalized or had any other serious illnesses. If so, additional details will be obtained regarding this illness, including medical records if possible. Volunteers will also be reminded to notify the investigators if they develop an autoimmune disease in the future and will be given contact information for such notification. In the US only SAEs or events possibly relating to autoimmune disease will be captured during the extended follow up period.

**Study Day 120 ±14 Days (Day of Third Vaccination) (Mali)**

1. Perform basic history and focused physical examination, emphasizing examination of any acute complaints.
2. During the physical examination, study staff will educate the subject regarding signs and symptoms of potential AEs, and indications for use of antipyretics (acetaminophen/paracetamol, or ibuprofen) if fever, headache, or malaise occurs.
3. Obtain approximately 35 mL of blood for CBC with differential and platelet count, ALT, creatinine, anti-AMA1 and anti-MSP142 antibody ELISA, and B cell studies.
4. Obtain blood for malaria smear and filter paper collection
5. For females, obtain a urine or serum sample for  $\beta$ -hCG testing. Ensure that the test is negative before vaccinating; a positive test will exclude the subject from the trial.
6. Obtain a urine sample for dipstick testing and ensure that protein and blood are no more than trace positive before vaccinating. Should a female subject be menstruating on the day of vaccination, she will not be excluded from vaccination if she has more than trace blood in her urine.
7. Obtain urine for chloroquine testing.
8. Record vital signs (blood pressure, temperature, heart rate, and respiratory rate).
9. Administer the vaccine.
10. Observe for at least 30 minutes after vaccination to evaluate for immediate adverse reactions.

**Study Day 121 (Mali only) (1 Day after Third Vaccination) (Mali)**

1. Perform basic history and focused physical examination (including injection site), emphasizing examination of any acute complaints.
2. Record vital signs.

**Study Day 122 (Mali only) (2 Days after Third Vaccination) (Mali)**

1. Perform basic history and focused physical examination (including injection site), emphasizing examination of any acute complaints.
2. Record vital signs.

**Study Day 123 ±1 Day (3 Days after Third Vaccination) (Mali)**

1. Perform basic history and focused physical examination (including injection site), emphasizing examination of any acute complaints.
2. Record vital signs.
3. Obtain approximately 10 mL of blood for CBC with differential and platelet count, ALT, and creatinine.
4. Obtain urine for dipstick test

**Study Day 127 ±1 Day (7 Days after Third Vaccination) (Mali)**

1. Perform basic history and focused physical examination (including injection site), emphasizing examination of any acute complaints.
2. Record vital signs.
3. Obtain urine for dipstick tests.
4. Obtain approximately 50 mL of blood for CBC with differential and platelet count, and B and T cell studies and serum creatinine.

**Study Day 134  $\pm$ 2 Days (14 Days after Third Vaccination) (Mali)**

1. Perform basic history and focused physical examination (including injection site), emphasizing examination of any acute complaints.
2. Record vital signs.
3. Obtain urine for dipstick testing. Obtain urine or serum for  $\beta$ -hCG testing.
4. Obtain approximately 40 mL of blood for CBC with differential and platelet count, ALT, creatinine, anti-dsDNA, anti-AMA1 and anti-MSP142 antibody ELISA, B and T cells, and GIA.
5. Obtain blood for malaria smear and filter paper collection

**Study Day 150  $\pm$ 3 Days (Mali)**

1. Perform directed history and assessment of any physical complaint.
2. Record vital signs.
3. Obtain urine for dipstick testing.
4. Obtain blood for malaria smear and filter paper collection

**Study Day 180  $\pm$ 7 Days (Mali)**

1. Perform directed history and assessment of any physical complaint.
2. Record vital signs.
3. Obtain blood for malaria smear and filter paper collection.

**Study Day 210  $\pm$ 14 Days (Mali)**

1. Perform directed history and assessment of any physical complaint.
2. Record vital signs.
3. Obtain urine for dipstick testing.
4. Obtain approximately 5 mL of blood for anti-AMA1 and anti-MSP142 antibody ELISA.
5. Obtain blood for malaria smear and filter paper collection.

**Study Day 240  $\pm$ 7 Days (Mali )**

1. Perform directed history and assessment of any physical complaint.
2. Record vital signs.
3. Obtain blood for malaria smear and filter paper collection

**Study Day 270  $\pm$ 7 Days (Mali)**

1. Perform directed history and assessment of any physical complaint.
2. Record vital signs.
3. Obtain blood for malaria smear and filter paper collection.

**Study Day 360  $\pm$ 14 Days (Mali)**

1. Perform directed history and assessment of any physical complaint.
2. Record vital signs.
3. Obtain urine for dipstick tests.
4. Obtain approximately 50 mL of blood for anti-dsDNA, anti-AMA1 and anti-MSP142 ELISA, GIA, and T and B cell studies.
5. Obtain blood for malaria smear and filter paper collection

**Study Day 720 ± 14 Days (Mali)**

An additional visit to the study clinic will be made and the volunteer will be asked about the development of any autoimmune disease or other serious illness and given contact information should an autoimmune disease develop, as above. Adverse events occurring during the extended passive follow up period will be captured as per usual in Mali.

**SYMPTOM MEMORY ENHANCEMENT TOOL (US ONLY)**

Subjects will be asked to keep daily symptom diaries recording oral temperature once during the day, as well as pain, tenderness, redness, swelling at the injection site and any systemic signs or symptoms for 6 days following each immunization. The size of any injection-site reaction will be measured using a standardized clear plastic measurement device and recorded in the symptom diary. Clinical site staff will review these diaries and record on the source document the daily temperature, injection site erythema, induration, pain and any other systemic sign or symptom noted by the subject. The diaries will not be collected.

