#### 1.1.12 Clinical Experience with BSAM-2/Alhydrogel+CPG 7909 to date

The Phase 1 study of BSAM-2/Alhydrogel®+CPG 7909 described in this protocol began vaccinations at the Center for Immunization Research, Washington, DC, in June, 2009. As of September 30, 2009, a total of 30 malaria naïve US volunteers have been enrolled to receive up to 3 doses of either 40 or 160 µg BSAM-2 with 560 µg CPG 7909. Local adverse events have been as expected, with mild or moderate injection site pain. Systemic adverse events after first or second vaccination have reached Grade 3 severity in 4 volunteers (Grade 3 malaise in 2 volunteers, and Grade 3 fever and headache in 2 additional volunteers). Two volunteers have been withdrawn from vaccinations due to these adverse events. The events typically occur within 24 hours of vaccination and resolve within several hours of administration of acetaminophen or ibuprofen. Transient mild or moderate neutropenia has also been seen, as in previous studies with CPG 7909.

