### 13. DATA HANDLING AND RECORD KEEPING

#### SOURCE DOCUMENTATION

Paper CRFs will be used at the Mali site and CRIMSON will be used at the US site. Study data will be collected on case report forms (CRFs) designed for the study and study-specific databases.

Complete source documentation (laboratory test reports, hospital or medical records, progress notes, observations, subject diaries, etc.) is required for every study subject for the duration of the study. The subject's medical record must record his/her participation in the clinical trial and, after unblinding, the randomization treatment received (with doses and frequency) or other concomitant medications or interventions administered, as well as any adverse reactions experienced during the trial. Data from source documentation and volunteer symptom diaries for subjects enrolled in the study will be entered into the CRIMSON Data System. The data entry is to be completed on an ongoing basis during the study. Data entered into CRIMSON shall be performed by authorized individuals. Corrections to the data system shall be tracked electronically (password protected) with time, date, individual making the correction, and what

was changed. Source documentation should support the data collected in CRIMSON, and must be signed and dated by the person recording and/or reviewing the data.

The Investigator is responsible for the accuracy, completeness and timeliness of the data reported to the Sponsor in the CRIMSON Data System. All data entered into CRIMSON should be reviewed by the Investigator and signed as required with written or electronic signature, as appropriate. Data reported in CRIMSON should be consistent with source documents or the discrepancies should be explained. Source documentation will be made available for review or audit by the Sponsor or designee and any applicable Federal authorities.

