## APPENDIX C: TOXICITY TABLE

| Local Adverse Event          | Grade | Intensity                                                                     |
|------------------------------|-------|-------------------------------------------------------------------------------|
| Pain at injection site       | 1     | Pain that is easily tolerated                                                 |
|                              | 2     | Pain that interferes with daily activity or treatment given                   |
|                              | 3     | Pain that prevents daily activity                                             |
| Erythema at injection site   | 1     | >0 mm - ≤20 mm                                                                |
|                              | 2     | >20 mm - ≤50 mm                                                               |
|                              | 3     | >50 mm                                                                        |
| Swelling at injection site   | 1     | >0 mm - ≤20 mm                                                                |
|                              | 2     | >20 mm - ≤50 mm                                                               |
|                              | 3     | >50 mm                                                                        |
| Induration at injection site | 1     | >0 mm - ≤20 mm                                                                |
|                              | 2     | >20 mm - ≤50 mm                                                               |
|                              | 3     | >50 mm                                                                        |
| Solicited Adverse Event      | Grade | Intensity                                                                     |
| Fever (oral)                 | 1     | 100.4°F – 101.5°F (38.0°C – 38.6°C)                                           |
|                              | 2     | 101.6°F – 102.4°F (38.7°C – 39.1°C)                                           |
|                              | 3     | ≥102.5°F (≥39.2°C)                                                            |
| Headache                     | 1     | Headache that is easily tolerated                                             |
|                              | 2     | Headache that interferes with daily activity, or treatment given              |

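### Section 6.6 names different local reactions for the US diary and for its transcription, and contradicts Section 13.1 on whether diaries are kept

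*Protocol*

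**What the plan says.** The primary endpoint is the incidence and severity of local and systemic adverse events (Study Endpoints). For US subjects, Section 6.6 (Symptom Memory Enhancement Tool) sets up a daily diary for 6 days after each dose, "recording oral temperature once during the day, as well as pain, tenderness, redness, swelling at the injection site", plus systemic signs and symptoms. It adds: "The size of any injection-site reaction will be measured using a standardized clear plastic measurement device and recorded in the symptom diary". Staff review the diary and are told to "record on the source document the daily temperature, injection site erythema, induration, pain and any other systemic sign or symptom noted by the subject". The section ends: "The diaries will not be collected".

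Appendix C has a row for "Swelling at injection site" and a separate row for induration, each graded by millimetres.

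Section 13.1 (Source Documentation) says: "Complete source documentation (laboratory test reports, hospital or medical records, progress notes, observations, subject diaries, etc.) is required for every study subject". It also has data from volunteer symptom diaries entered into CRIMSON.

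**The concern.** The list that the subject fills in and the list that staff copy from it should be the same list, and both should match the grading table. Here they differ on three local items. Staff who follow the transcription rule literally would leave out a swelling measurement, or enter it under the nearest listed term, induration. Either choice alters the local adverse-event tables that address the primary objective.

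The retention conflict makes this harder to repair. If the diary stays with the subject, the staff transcription is the only surviving record of the home measurements. An omitted or relabelled entry could then be neither found nor corrected. The Site Monitoring Plan has monitors compare subject records with source documents. Without the diary, that comparison stops at the transcription.

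The diary carries particular weight in the US. Mali participants are examined on Days 1 and 2 after each dose. US participants are next scheduled on Day 3 (±1) after the 30-minute observation, so in between the diary is the only scheduled record of a local reaction.

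**Working it through.** No plan figure is in dispute. The sample-size statement (12 per group, event probability 0.125, detection probability 0.80) reproduces as 1 − 0.875^12 = 0.7986. It assumes that an event that occurs is also recorded. The check itself compares texts.

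**Step 1. Local items, side by side.**

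| Local item | Diary (6.6) | Staff transcription (6.6) | Appendix C |
|---|---|---|---|
| Pain | named | named | own row |
| Tenderness | named | not named | no row |
| Redness / erythema | named | named | own row, mm |
| Swelling | named | not named | own row, mm |
| Induration | not named | named | own row, mm |

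Only pain and erythema agree across all three. The closing words of the transcription rule extend to other systemic findings. Swelling and tenderness are local, so those words do not bring them in.

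**Step 2. Can induration stand for swelling?** Appendix C uses the same cut-points for both: Grade 1 up to 20 mm, Grade 2 above 20 to 50 mm, Grade 3 above 50 mm. A swelling entered as induration would keep its grade but move to another event type, so swelling would be under-counted and induration over-counted. A swelling left out would remove both the event and its grade. One entered under both names would add an event.

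**Step 3. Which analyses are touched?** Section 11.1.1 (Primary Objective) summarises local adverse events by severity, compares the proportion of subjects with at least one event, and applies a sign test to the number of events in the 2 weeks after each vaccination. Relabelling affects the tables by event type. Omission or double entry affects the counts in the sign test. The proportion with at least one event changes only for a subject whose sole event was the omitted one.

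**Step 4. Retention.** Section 6.6 leaves the diary uncollected. Section 13.1 requires subject diaries among the source documents of every subject. A site cannot do both.

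**Step 5. Extent.** The diary is US-only: 30 of 60 participants (one half). With up to 3 doses each, at most 30 × 3 = 90 diary periods are involved, and fewer in practice, because Section 1 reports two US volunteers withdrawn from vaccinations.

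**The case against.** The strongest reply is that the protocol has other ways to catch these reactions. Section 9 has adverse events elicited and documented at every contact, and requires all local and systemic reactions on the CRF. Staff examine the injection site on Days 3, 7 and 14 after each dose and review the diary at the first two of those visits. The diary also takes the size of any injection-site reaction, which can include induration. This stands. It rules out saying that induration is never recorded or that swelling has no path to the record. It does not remove the mismatch, because the general rule does not say how a home swelling measurement is to be transcribed, and the one rule that does omits it.

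A second reply is that the staff-completed source document is the intended record and the diary only a memory aid. That is a coherent design, and the CRF can still be checked against that document. But Section 13.1 says otherwise, so one of the two texts must change.

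A third reply is timing. Section 1 reports 30 US volunteers enrolled by 30 September 2009, with events after first or second vaccination already described. A correction reaches only the doses still to come, and the earlier diaries only if they survive.

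A reader might also infer that one temperature reading a day misses fever peaks, since Section 1 says of the Grade 3 systemic events: "The events typically occur within 24 hours of vaccination and resolve within several hours of administration of acetaminophen or ibuprofen". The documents do not support making that a defect. Once-daily reading is a stated design choice that contradicts nothing, and Grade 3 fever had already been detected in two US volunteers. The quoted time is time to resolution after an antipyretic, not the duration of fever, so any miss rate would rest on assumed durations and reading times. More frequent readings introduced part-way would also raise detection after later doses only and could bias the sign test.

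**Conclusion.** Two defects hold on the text alone. First, the diary list, the transcription list and Appendix C do not agree on swelling, tenderness and induration. Second, Sections 6.6 and 13.1 contradict each other on the diaries. The exposure is limited to US participants, and within them to the daily size and peak grade of swelling between visits, or its misclassification as induration, without an original entry to recheck. The conclusion assumes that staff apply the transcription list as written. If site practice already copies every local reaction, the harm is confined to the protocol text and the source conflict.

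No rate of lost events can be given. A reader might count the days without a clinic examination as days without data, but diary entries for those days are reviewed at the visits, so that count would overstate the gap. Nor does this point show that the halting rules are weakened: the fourth rule counts laboratory abnormalities and Grade 3 systemic events, and swelling is neither. The correction is modest, but worth making because it concerns primary-endpoint severity data and costs almost nothing.

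**What to change.** In Section 6.6, use one item list for the diary card, the staff transcription and the grading: pain, tenderness, erythema, swelling, induration and the named systemic events of Appendix C. Since Appendix C has no tenderness row, state how tenderness is graded. Replace the sentence on not collecting diaries with one that retains the diary, or a certified copy, as source, so that Sections 6.6 and 13.1 agree.

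For doses already given, check whether the diaries still exist and how swelling was transcribed. If it was handled differently before and after the change, report this beside the sign test, because a change in recording between doses can look like a change in event counts.

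The cost is revised card and CRF wording and the filing of one diary per dose. No visits, measurements or staff are added.
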